# Clinical evaluation of paraspinal mini-tubular technique vs. laminoplasty for spinal intradural extramedullary tumors: Study protocol for a multicenter, randomized controlled trial

**DOI:** 10.3389/fsurg.2022.1053885

**Published:** 2023-01-05

**Keywords:** paraspinal minitubular technique, laminoplasty, randomized controlled trial, intradural extramedullary, multicenter

## Abstract

**Trial registration number:**

ChiCTR2100047582

## Introduction

1.

Although spinal intradural extramedullary (IDEM) tumors grow slowly, the spinal canal is limited by its small volume, and the spinal cord and nerve roots are compressed or invaded by the tumor, which causes sensory, motor, and autonomic dysfunction (1). The treatment of spinal IDEM tumors focuses on removing tumor tissue and decompressing the nerve root and spinal cord to improve nerve function (2, 3). Traditional surgical methods include laminectomy (total laminectomy and hemilaminectomy), laminotomy, and laminoplasty (LP) (4). Among the available spinal surgeries with different indications, a “standard surgical procedure” for treating spinal IDEM tumors has not been determined. Owing to the development of minimally invasive spine surgery (MISS), the paraspinal mini-tubular technique (PMTT) has been introduced for treating IDEM tumors (5–7). Most studies reported that tubular spine surgeries reduced the volume of estimated blood loss (EBL) and shortened the length of hospital stay. The postoperative outcome of the patients was good, with fewer complications. These together promoted the development of MISS. A microscope-assisted PMTT has a larger operating space than endoscopy and a relatively wide range of indications, including various types of intervertebral disc herniation, spinal stenosis, spinal tumors, and spinal cord injuries (8). With the popularization and application of PMTT, the safety and effectiveness of treating spinal-related diseases have been increasingly recognized. Compared with traditional surgery, the microscope-assisted microtubular technique has the advantages of less tissue damage, fewer complications, shorter length of hospital stay, reduced postoperative pain, improved surgical efficiency, and reduced risk of spinal instability (9–11). To the best of our knowledge, prospective, randomized controlled trial studies with a large sample comparing the safety and effectiveness of the PMTT and LP in the treatment of spinal IDEM tumors, have not been conducted. Therefore, this study aims to explore the difference in the therapeutic effect of the PMTT and LP in the treatment of patients with spinal IDEM tumors through a prospective, multi-centered, non-inferiority randomized clinical trial. The main hypothesis is that PMTT has advantages in cost-effectiveness, and it is equivalent in safety and efficacy to LP.

## Methods and analysis

2.

### Study description

2.1.

The FJMUUH05 trial is designed as a prospective, multi-center, non-inferiority RCT with two parallel groups in eight hospitals from seven provinces in China. A total of 280 patients aged 10–75 years with confirmed radiographic diagnosis and IDEM tumor lengths of less than three segments will be enrolled in this study. After the patients sign a written informed consent to participate, they will be randomized to one of the two groups: the PMTT group, which will receive paravertebral approach and microtubular technique treatment, and the LP group, which will receive laminoplasty treatment. The follow-up period will last for two years. The study is registered at https://www.chictr.org.cn, which can be accessed online (ChiCTR2100047582). Consent (version date January 21, 2021, V.1.0) will be obtained by an investigator who will comply with applicable regulatory requirements and adhere to the ethical principles of the Declaration of Helsinki. The time points, randomization, treatment allocation, and assessment are summarized in Figure 1.

**Figure 1 F1:**
[figure not shown]
The schedule of enrolment, interventions, and assessments. *PMTT group, paraspinal mini-tubular technique; LP group, laminoplasty group.

### Participant eligibility and recruitment

2.2.

Participating surgeons and hospitals must satisfy the following criteria to prevent bias: surgeons must have experience performing >100 surgeries for spinal tumors, participating hospitals should have performed >40 spinal tumor surgeries annually, and they must have completed the Fujian Medical University Union Hospital spinal training program.

Eligible patients with spinal IDEM tumors will be referred by the participating surgeons, following a formal outpatient assessment. This study follows the informed consent principle; thus, each patient must provide written informed consent prior to group randomization. Detailed inclusion and exclusion criteria are listed in Table 1.

**Table 1 T1:** Selection criteria for trial eligibility.

Inclusion criteria:
Age 10–75 years
Spinal IDEM tumors confirmed by clinical symptoms and radiographic findings
Magnetic resonance imaging with the length of the tumor less than three segments
The patient has given oral and written informed consent to participate
Exclusion criteria
Spondylitis or degenerative spondylolisthesis
Previous surgery on the same or adjacent spinal level
Severe somatic or psychiatric illness
The patient fails to be present in the follow-up appointments required by the protocol, or the investigator deemed that the risk of patients in the study increases
The patient cannot provide written informed consent or cannot follow the trial
The survival period of the patient is <1 year

### Patient and public involvement statement

2.3.

The patients and public are not involved in the design, conduction, reporting, or dissemination plans of this research.

### Randomization and blinding

2.4.

Once written informed consent is obtained, patients would be randomized to undergo either the paravertebral approach or microtubular technique, or LP in a ratio of 1:1. The patients will be randomized using a block randomization model (block size: six). Computer-generated random number tables will be prepared by an experienced statistician. After baseline data are obtained, and a physical examination has been conducted, allocation of treatment will be performed by the computer system, and the results of the allocation will be provided to the surgeon in a concealed envelope one day before surgery. Due to the noticeable differences between the PMTT and LP procedures, blinding of the patients will not be strictly required. However, all researchers and data analysts will be blinded to the allocated intervention during the follow-up period of 2 years.

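### One fixed, disclosed block size of six, with unblinded surgeons who refer the patients, weakens allocation concealment if blocks run within centres

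*Protocol article*

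**What the plan says.** Section 2.4 (Randomization and blinding) of the protocol article sets "LP in a ratio of 1:1" and fixes a single block size: "The patients will be randomized using a block randomization model (block size: six". It gives no second size and no random variation of size.

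The same section and section 2.2 (Participant eligibility and recruitment) describe who knows what, and when:

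- Selection: "Eligible patients with spinal IDEM tumors will be referred by the participating surgeons, following a formal outpatient assessment". Table 1 also lets the investigator exclude a patient whose risk in the study is judged to increase.
- Sequence: "Computer-generated random number tables will be prepared by an experienced statistician", and "allocation of treatment will be performed by the computer system" once baseline data and a physical examination are complete.
- Consent: "each patient must provide written informed consent prior to group randomization".
- Disclosure: "the results of the allocation will be provided to the surgeon in a concealed envelope one day before surgery".
- Blinding: patients need not be blinded. Researchers and analysts are to be blinded during the two-year follow-up. The operating surgeon cannot be.

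Section 2.1 gives eight hospitals and 280 patients. Section 2.11 says recruitment began in October 2021 and was intended to take two years. The article is dated 5 January 2023. It does not say whether blocks run within each centre or on one central list.

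**The concern.** Permuted blocks force balance at known points. A person who knows the block size and has seen the earlier allocations in a block can tell which arm is under-represented, and near the end of the block can sometimes tell the next arm with certainty. Here the people who decide whom to refer, and when, are the same people who open the envelopes and operate.

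The stated safeguards protect the assignment of the patient now being enrolled. They act after referral, whereas inference from past allocations acts at referral. A surgeon who expected a particular arm next could, deliberately or not, delay or redirect a tumor judged difficult for that technique. The arms would then differ in prognosis for reasons unrelated to treatment. In a non-inferiority trial such a shift could produce a false non-inferiority conclusion or hide a true one.

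**Working it through.** The plan gives no figure for predictability, so there is none to reproduce.

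**Inputs.** Block of six and 1:1 ratio, hence 3 + 3 (section 2.4). 280 patients and eight hospitals (section 2.1). Equal centre size is an assumption: 280 / 8 = 35.

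**Step 1: one fully observed block of six.** There are C(6,3) = 20 equally likely orderings. An allocation is certain when one arm already has its three patients. The best guess is the arm with more places left, or a coin toss when the two are equal.

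| Position | Probability certain | Probability best guess is right |
|---|---|---|
| 1 | 0 | 0.5 |
| 2 | 0 | 3/5 = 0.6 |
| 3 | 0 | 0.4 × 3/4 + 0.6 × 1/2 = 0.6 |
| 4 | 2/20 = 0.10 | 0.1 × 1 + 0.9 × 2/3 = 0.7 |
| 5 | 8/20 = 0.40 | 0.4 × 1 + 0.6 × 1/2 = 0.7 |
| 6 | 1 | 1 |
| Sum | 1.5 | 4.1 |

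Certain: 1.5 / 6 = 25%. Correct guesses: 4.1 / 6 = 68.3%, against 50% by chance.

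**Step 2: scale to the trial, with lists within centres.**

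- Complete blocks only: 0.25 × 280 = 70 certain allocations.
- Eight centres of 35, each with five full blocks and five patients of a sixth: 5 × 1.5 + (0.10 + 0.40) = 8.0 per centre. That is 8.0 / 35 = 22.9%, and 8 × 8.0 = 64 in total.
- Best guessing in 35 patients: (5 × 4.1 + 3.1) / 35 = 67.4%.

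These counts are upper bounds. They assume that one team sees every allocation, tracks block boundaries and knows the size from the first patient on.

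**Step 3: one central list.** Simulation: fixed blocks of six, 280 patients spread at random over eight equal centres, each guessing from its own past allocations only. Correct guesses: 50.8%.

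**Step 4: effect of varying the size.** Simulation: 35 patients per centre, sizes 4, 6 and 8 drawn with equal probability. The observer knows this set but not the size drawn.

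| Within-centre list, 35 patients | Certain | Best guess right |
|---|---|---|
| Fixed six | 22.9% | 67.4% |
| Random 4/6/8 | about 2% | 67.3% |

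The gain is therefore almost entirely in the certain predictions. A 6/8/10 mix lowers the guess rate only to 65.6%.

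**Step 5: timing.** From October 2021 to publication in January 2023 is about 15 of the 24 planned months, so publication itself could inform only about the last 9. Whether surgeons knew the size earlier is not stated.

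**The case against.** A reader might infer that upcoming allocations are predictable and that the comparison is thereby broken. The article does not support that, for these reasons:

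- **List structure.** Nothing says that blocks run by centre. A statistician's tables and a computer system fit one central list at least as well, and there guessing is near chance. A condensed article may leave this detail to the full protocol, so the worst case must not be assumed. This stands, and makes the size of the concern conditional.
- **What the surgeon sees.** The text supports knowledge of the surgeon's own cases, not of every past allocation. With several surgeons at a centre, prediction weakens unless they share information. This stands.
- **Existing safeguards.** Consent, baseline assessment and computer allocation already come before disclosure. They protect the current assignment but do not act on referral, so they answer the point only in part.
- **Repair by analysis.** JOA, VAS and tumor location are recorded before randomization (section 2.6), so imbalance in these can be seen and adjusted for. It would be too strong to say that no analysis can help. What may remain is selection on surgical difficulty that these variables do not capture.
- **Limited remedy.** A surgeon who steers on best guesses is almost unaffected by varying the size. This stands.
- **Early stage.** The Discussion counts 11 patients, but dates that to October 2021, the month recruitment opened. It cannot be taken as the number enrolled at publication.

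The document offers no evidence that steering has occurred, and its direction could favour either technique.

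**Conclusion.** The point holds as a conditional weakness in a stated design choice. A single block size, made public during planned recruitment, is a poor fit for a trial in which the operating surgeons select the patients and know their own past allocations.

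Its size runs from negligible to material. On a central list whose other allocations sites cannot see, correct guessing is about 51%. With within-centre lists and a team that sees the whole block, up to a quarter of allocations are certain and about 68% can be guessed. The count of 64 to 70 patients is a ceiling, not an estimate. The consequence is a risk of selection bias, not a demonstrated bias. The change is worth making because it is cheap and a fixed, disclosed size offers little in return beyond slightly tighter balance.

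**What to change.** For all remaining patients, replace the fixed block of six with centrally generated permuted blocks of randomly varying size (for example 4, 6 and 8), and do not disclose the sizes to sites or surgeons. A sentence saying whether the list is central or by centre would let readers judge which end of the range applies.

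The cost is regenerating the unused part of the list and amending one sentence. Balance may be slightly looser when a list stops mid-block: the largest possible difference is half a block, so 4 for a block of eight against 3 for a block of six. The change cannot help patients already allocated, and the article does not state how many there were at publication.

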### Treatment

2.5.

Patients will be randomized to receive either PMTT or LP treatments. The tumor's location will be verified using a mobile image intensifier with fluoroscopy (anteroposterior and lateral views). The PMTT and LP will be performed under general anesthesia. All the patients will be placed in a standard prone position. The surgeons involved in this study would have had extensive experience with both procedures.

#### (A) intervention: PMTT

2.5.1.

After inducing general anesthesia, the patients will be placed in the prone position to minimize lumbar lordosis or thoracic kyphosis and to avoid compressing the abdomen. A 20–25 mm skin incision will be made approximately 20–35 mm lateral to the midline (adjusted according to the patient's body habitus), and the accurate target level will be confirmed by lateral fluoroscopy. The paravertebral approach will involve the paraspinous muscles, and the muscles will be bluntly dissected by a muscle-splitting technique. After the smallest dilator is inserted to reach the lamina or peripheral bone structure, the dilators will be piled sequentially, and the working tubule (diameter, 14 or 16 mm) will be inserted over the dilators. The dilators will be removed, and a tubular surgical channel will be established. The tubule will be fixed using a flexible fixed arm mounted on the operating table. The tubule could be angulated to expand the operating field because of the flexible fixed arm. The subsequent procedure will be performed under a microscope (OPMI Pentero, Carl Zeiss, Germany). Part of the lamina will be removed using high-speed drills and Kerrison rongeurs. After the dura mater is incised, the IDEM tumor will be separated and removed piece by piece using a microsurgical technique. The dura mater will be sutured tightly. After the tubule is withdrawn, the paravertebral muscles will be repositioned, and the fascia, subcutaneous tissues, and skin will be sutured in sequence. Thereafter, a surgical drain will be placed in the resection site for 24–48 h.

#### (B) intervention: LP

2.5.2.

A skin incision will be made, and subcutaneous tissue, lower back fascia, and muscle will be incised in layers to expose the spinous process and lamina of the spinal segment where the tumor is located. The retractor will be used to expose the bone structures, and the complex of the spinous process and lamina will be removed using an ultrasonic bone knife combined with a high-speed drill. The ligamentum flavum will be removed, and the dura will be sharply incised. The tumor will be separated and removed with the aid of a microscope, and the dura will be closed with a 5.0 or 6.0 suture. The spinous process and lamina will be repositioned, and the laminoplasty will be performed with titanium screws and connecting plates. The paravertebral muscles will be repositioned, and the fascia, subcutaneous tissue, and skin will be sutured one after the other. A drain will be placed at the resection site for 24–48 h.

### Baseline assessment

2.6.

The demographics, medical history, family history of tumors, results of a physical examination, body mass index, tumor location, visual analog scale (VAS) scores, and Japanese Orthopedic Association (JOA) scores will be recorded at baseline. Data will be collected prior to randomization.

### Withdrawal

2.7.

All patients can decide to withdraw at any time. If a patient withdraws, information will not be recorded in the study. However, the research team can still collect the outcome data from the healthcare records.

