### Outcome measurements

2.8.

Patients must have an indication for the surgery. The primary outcome variable is the JOA score. The secondary outcome variables include the VAS score, physical examination findings, length of hospital stay, expenses, and complications. Outcomes will be measured on the first postoperative day, and thereafter at the 1st week, and at 1, 3, 6, 12, and 24 months after surgical treatment. A physical examination will be conducted after 1 week, 1 month, and 12 months from the day of the surgery (Table 1). The non-inferiority margin for the primary outcome is five.

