### Statistical analysis

2.12.

All data will be analyzed according to the intention-to-treat principle (16, 17). The baseline data will be compared and analyzed using descriptive statistics [mean (SD), proportion, or median (range)] to determine whether balanced groups were obtained after randomization. Student's *t*-test or Mann–Whitney's *U* test will be used to compare continuous variables. Categorical variables will be compared using *χ*^2^ or Fisher's exact tests. All comparative analyses will be reported with point estimates [means (SD) or odd ratios (ORs)], 95% CIs, and *p*-values. Statistical significance will be set at *p *< 0.05. Non-inferiority margins will be set as listed in Table 2. Statistical analysis will be performed using appropriate statistical software (e.g., SPSS version 22.0 or Stata).

**Table 2 T2:** Non-inferiority margins.

Outcome measurements	Expected differences	Non-inferiority margin
JOA	<5	5
VAS	<5	5
muscle strength test	<5	5
Sphincter function test	<5	5

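### The withdrawal rule and the attendance exclusion conflict with the promise to analyse all data by intention-to-treat

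*Protocol article*

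**What the plan says.** Four places in the protocol article bear on which randomized patients contribute to the primary comparison.

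- Section 2.12 (Statistical analysis): "All data will be analyzed according to the intention-to-treat principle".
- Section 2.7 (Withdrawal): "If a patient withdraws, information will not be recorded in the study". The next sentence adds: "However, the research team can still collect the outcome data from the healthcare records".
- Section 2.2, Table 1, under the exclusion criteria: "The patient fails to be present in the follow-up appointments required by the protocol". The same line adds an investigator's judgement that the risk to patients in the study has increased.
- Sections 2.8 and 2.9: "The primary outcome variable is the JOA score", and the questionnaire data are gathered by a research nurse at fixed times up to 24 months after surgery.

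The trial is described in Section 2.1 as a "prospective, multi-center, non-inferiority RCT with two parallel groups in eight hospitals from seven provinces in China". Section 2.11 allows for 10% attrition.

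**The concern.** Intention-to-treat means that every randomized patient stays in the comparison, in the arm to which he or she was allocated, whatever happens later. An exclusion triggered by missed visits and a rule that withdrawn patients' information is not recorded both act after allocation. If site staff apply them as written, the analysis described in Section 2.12 cannot be carried out, because the outcomes it needs will not exist.

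Loss of this kind need not be balanced. Section 2.4 does not strictly require patients to be blinded, so a patient may know the procedure received when deciding whether to keep attending. Patients who stop attending may differ in function from those who continue. The comparison of mean JOA would then rest on a selected subset in each arm, and the selection could differ between arms. An outcome that was never recorded cannot be restored at the analysis stage.

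**Working it through.** **Step 1. The provisions side by side.**

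| Provision | When the deciding fact is known | Effect on a randomized patient if followed literally |
|---|---|---|
| Section 2.12, intention-to-treat | At randomization | Stays in the analysis |
| Table 1, missed follow-up | Weeks to two years after surgery | Excluded |
| Section 2.7, first sentence on recording | At withdrawal | Not recorded |
| Section 2.7, following sentence | After withdrawal | Outcome may be taken from records |

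The second and third rows cannot both be followed together with the first. The third and fourth rows also pull against each other, and the fourth is a permission, not a requirement.

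**Step 2. Can the records route supply the primary outcome?** Section 2.9 obtains the questionnaire data through a research nurse at study time points. Nothing in the article says that routine records hold a JOA score. The route may therefore serve for complications or length of stay and still leave JOA missing.

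**Step 3. What the plan's attrition figure covers.** Section 2.11 needs 112 per group, 224 in total. With 10% attrition, 224 / 0.90 = 248.9, so 249. The planned 280 leaves room for 1 − 224/280 = 20%; the article attributes the increase to attrition and to the situation of the centres. This protects the number of patients analysed. It does nothing about who is lost.

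**Step 4. Size of the shift (illustration).** Let a fraction L of one arm be lost, with mean JOA lower by g than the patients retained. The arm's full mean is (1 − L)·m + L·(m − g) = m − L·g, where m is the mean of those retained. Using retained patients only overstates the arm by L·g.

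| L | g (assumed) | Shift in JOA points |
|---|---|---|
| 10% | 2 | 0.2 |
| 10% | 5 | 0.5 |
| 10% | 8 | 0.8 |
| 20% | 5 | 1.0 |

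L = 10% is the plan's attrition figure, here placed in one arm only. The gaps g are assumptions; the document gives none.

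**Step 5. Direction.** A higher JOA score is better. Loss of poorer patients from PMTT raises the observed PMTT mean and helps non-inferiority. The same loss from LP raises the LP mean and works against it. Equal loss with equal gaps in both arms cancels.

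For scale, take a true PMTT deficit of exactly 5, SD 5.8 (Section 2.11), 140 per arm (280 at 1:1), 10% lost from one arm so that 126 remain, and a one-sided level of 0.025. The last is an assumption, because the article gives alpha 0.05 without stating sides.

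- SE = 5.8 × √(1/126 + 1/140) = 0.712.
- Loss from PMTT, g = 5: Φ(0.5/0.712 − 1.96) = Φ(−1.26) = 10.4% false non-inferiority, against 2.5% nominal.
- Loss from LP, g = 5: Φ(−0.5/0.712 − 1.96) = Φ(−2.66) = about 0.4%.

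The same rule can thus push the error rate either way.

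**The case against.** The best defence is that these are loose phrases in a condensed article. Table 1 is an eligibility table, and the attendance item sits near one about patients who cannot follow the trial, so it may mean expected non-attendance. Section 2.7 can be read as ending study recording at withdrawal while outcomes continue through the records. Section 2.12 applies intention-to-treat to all data and could be taken to govern.

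Part of this stands. Nothing says that data already collected are erased, or that a withdrawn patient leaves the analysis set, so a reader who infers deletion goes beyond the text. But the attendance item is worded as something that happens, not something expected. A separate criterion already covers patients unable to follow the trial, and the rest of the line concerns risk to patients in the study. The defence also does not show how JOA would be obtained from records.

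Two stronger readings are tempting, and the document supports neither.

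- *Selective loss favours non-inferiority.* Step 5 shows that the direction depends on which arm loses its poorer patients, which the document does not indicate.
- *Reliance on intention-to-treat alone makes non-inferiority too easy because of conversions between procedures.* The article mentions no conversion and gives no rate, so any figure for this would be assumed. Naming intention-to-treat does not rule out a supportive per-protocol analysis, which may be in the analysis plan that is not shown. Requiring both analyses to clear the margin is a debated convention, and a set that drops converted cases also selects on a post-randomization event.

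**Conclusion.** The point holds as a contradiction within the document: Table 1 and Section 2.7 are wrong as written, given Section 2.12. That conclusion needs no assumption about the trial's results and does not depend on the unseen analysis plan.

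The size of any bias is not known. The 0.5-point shift, 10% of the margin of 5, rests on two assumptions: that the whole 10% loss falls in one arm, and that lost patients score 5 points worse. The direction is open. The error rates further assume a true deficit at the margin and a one-sided 0.025 test. The absence of a per-protocol analysis from this article is not an error.

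The correction matters despite the modest illustrative size, because it is nearly free and the missing outcomes could not be recovered later.

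**What to change.** Make three wording changes.

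1. Table 1: replace the attendance item with *judged before randomization to be unable to attend follow-up*. Tie the investigator's risk judgement in the same line to the time before randomization, so far as it decides who is in the trial.
2. Section 2.7: replace the recording sentence with *data collected up to withdrawal are kept and, unless consent to data use is withdrawn, later outcomes including JOA continue to be collected at visits the patient still accepts or from healthcare records*.
3. Section 2.12: state that all randomized patients are analysed as randomized.

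A per-protocol analysis may be reported as supportive; this point does not require it.

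The cost is an amendment, a check that the consent form covers continued collection, and some added effort by site staff to obtain JOA from patients who leave the visit schedule. No extra patients are needed. Recruitment began in October 2021, so the change should reach the sites promptly and apply, where consent allows, to patients already enrolled.
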